## Abstract

**Objective:**

To evaluate the efficacy of photobiomodulation (PBM) in reducing perineal pain and obstetric vulvar edema, as well os its effects on maternal functioning during the immediate postpartum period.

**Methods:**

This randomized, controlled, double-blind clinical trial protocol will include women aged over 15 years, within 12 h after vaginal delivery, presenting with first- or second-degree perineal trauma and/or vulvar edema and pain ≥ 3 on the Numeric Rating Scale. Participants will be randomized in blocks of four to receive PBM or a sham intervention alongside usual postpartum care. A single PBM session will be performed using 808-nm infrared laser light at an output power of 100 mW. Assessments will be performed at baseline, immediately after the intervention, 12 h, 40 days, and three months postpartum. Outcomes will include pain, pressure pain threshold, vulvar edema area, maternal functioning, treatment satisfaction, urinary incontinence, and sexual function. Statistical analysis will follow the intention-to-treat principle using linear mixed-effects models, with group, time, and group × time interaction as fixed effects and participant as a random effect. Post-hoc comparisons will use Bonferroni correction, with a significance level of 5%.

**Conclusion:**

PBM is expected to reduce perineal pain and vulvar edema and improve maternal functioning. The randomized design, sham control, blinded outcome assessment, and longitudinal analysis are expected to provide evidence regarding the efficacy and safety of PBM as a non-pharmacological strategy for postpartum care.

**Trial Registration:**

Brazilian Clinical Trials Registry (REBEC), RBR9sgdsm2, approved on July 7, 2026.

## Introduction

The pelvic floor (PF) is a complex structure composed of muscles, ligaments, and fascia that closes the inferior pelvic outlet and supports the pelvic organs. During pregnancy and vaginal birth, this structure is subjected to substantial biomechanical stress, predisposing women to pelvic floor disorders (PFDs) during the postpartum period [1]. 

Approximately 85% of women undergoing vaginal birth experience some degree of perineal trauma, including spontaneous perineal tears and/or episiotomy. Perineal tears are classified into four degrees according to the Royal College of Obstetricians and Gynaecologists and the American College of Obstetricians and Gynecologists. First- and second-degree tears are considered minor injuries, involving superficial tissues and the perineal muscles, whereas third- and fourth-degree tears are classified as severe because they involve the anal sphincter complex and the rectal mucosa [2]. 

In the short term, perineal trauma may result in pain, bleeding, wound complications, infection, and prolonged hospitalization. In the long term, it may lead to persistent pain, dyspareunia, urinary and fecal incontinence, fistula formation, and pelvic organ prolapse. [3–4] Severe perineal lacerations, particularly third- and fourth-degree tears, may substantially affect women’s quality of life and mental well-being, highlighting the importance of identifying risk factors and implementing preventive strategies during childbirth.4 In addition to these physical consequences, these conditions may adversely affect maternal functioning, quality of life, emotional well-being, and maternal–infant bonding during the postpartum period. [4–5]

Perineal trauma may also be associated with vulvar edema, a condition related to pregnancy-specific factors such as preeclampsia, diabetes, prolonged labor, operative vaginal delivery, hypoproteinemia, and anemia [6, 7]. Although its pathophysiology has not been fully elucidated, it is believed to involve alterations in hydrostatic and oncotic pressures, as well as the characteristics of the loose connective tissue of the vulva. Current treatment options are limited and predominantly pharmacological, including corticosteroids, hypertonic saline compresses, albumin, low-molecular-weight heparin, and antibiotics [8–10]. 

Photobiomodulation (PBM) has emerged as a promising non-pharmacological intervention because of its analgesic, anti-inflammatory, and anti-edematous effects. By stimulating mitochondrial chromophores, PBM enhances adenosine triphosphate production and modulates important biological processes, including inflammation, angiogenesis, lymphangiogenesis, and the release of endogenous opioids [11–13]. Although the body of evidence supporting PBM for pain management is growing, robust randomized controlled trials evaluating its effects on postpartum perineal pain and obstetric vulvar edema remain scarce.

Accordingly, this study protocol aims to describe a randomized clinical trial designed to evaluate the efficacy of photobiomodulation in reducing perineal pain during the postpartum period (change from baseline). Secondary objectives include evaluating vulvar edema, maternal functioning, urinary incontinence, sexual function, and patient satisfaction.

## Methods

### Study design

This study is a randomized, controlled, parallel-group, superiority, double-blind clinical trial designed to evaluate the effects of photobiomodulation (PBM) on perineal pain during the immediate postpartum period.

### Participants

The study population will consist of women aged over 15 years in the immediate postpartum period following vaginal birth who present with perineal trauma and/or obstetric vulvar edema and are admitted to the Pre-labor, Labor and Postpartum Unit, the Normal Birth Center, or the Surgical Ward of University Hospital. Eligible participants who provide written informed consent will be randomly assigned to one of the study groups.

#### Inclusion criteria

Women will be eligible if they meet all of the following criteria: age > 15 years; pain intensity ≥ 3 on the Numeric Rating Scale (NRS); first- and/or second-degree perineal trauma and/or vulvar edema; immediate postpartum period (up to 12 h afterchildbirth) (Table 1).

**Table 1 Tab1:** Participant timeline: Schedule of enrollment, interventions, and assessments

	Trial period			
Timepointb	Enrollment	Post-randomization		Close-out
	July 2025 to December 2026 T0	Post-immediate postpartum T1	after 12 h T2	40 days, and 3 monthst T3,T4
ENROLLMENT:				
Eligibility screen	x			
Informed consent	x			
Randomization				
INTERVENTION/ COMPARATOR:				
G1 – Photobiomodulation	x			
G2 – Sham PBM + Usual care				
ASSESSMENTS:		x		
Pain (NRS)	x			
Vulvar edema	x	x	x	
Immediate postpartum functioning	x	x	x	
Patient satisfaction	x	x	x	
Patient Global Impression of Change (PGIC)	x	x	x	
ICIQ-SF				x
WHODAS 2.0				x
FSFI				x
Adverse events	x	x	x	x

Abbreviations *PBM* photobiomodulation, *T0* pre-intervention, *T1* immediately after the intervention, *T2* 12 hours after the intervention, *T3* 40 days postpartum, *T4* 3 months postpartum, *NRS* Numeric Rating Scale, *WHODAS 2.0* World Health Organization Disability Assessment Schedule 2.0, *ICIQ-SF* International Consultation on Incontinence Questionnaire–Short Form, *FSFI* Female Sexual Function Index

#### Exclusion criteria

Women will be excluded if they present with vaginal wounds unrelated to perineal trauma, clinical signs or a confirmed diagnosis of vaginal infection, vulvar hematoma, cognitive impairment, or communication difficulties that preclude participation.

Eligible participants will be enrolled and randomized into one of two groups: photobiomodulation (G1) or sham photobiomodulation plus usual care (G2). The intervention will be delivered by physiotherapists with at least one year of clinical experience in pelvic floor physiotherapy and previous training in photobiomodulation. All therapists will undergo standardized training before the initiation of the study.

### Sample size calculation

The sample size was calculated using G*Power software (version 3.1.9.7), based on a two-tailed independent-samples Student’s *t* test for the comparison of means between two independent groups. A significance level of 5% (α = 0.05), statistical power of 80% (1 − β = 0.80), and an allocation ratio of 1:1 were assumed. Based on the findings of Alvarenga et al. ^16^. a mean perineal pain score of 4.5 (SD = 3.0) was assumed for the experimental group and 2.0 (SD = 2.2) for the sham group, resulting in an estimated effect size (Cohen’s *d*) of 0.784. The analysis indicated a minimum sample size of 54 participants, with 27 participants per group, achieving an actual statistical power of 80.75%. Considering an anticipated dropout rate of 20%, the sample size was increased to 68 participants, with 34 participants allocated to each group [14–16]. 

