### Participant characteristics and outcome assessments

Participants will undergo five assessments: three during the immediate postpartum period (baseline, immediately after the intervention, and 12 h after the intervention), one at 40 days postpartum, and one at 3 months postpartum. The schedule of assessments and assessment instruments is summarized in Table 3.

**Table 3 Tab3:** Detailed description of study outcomes

Outcome	Instrument/test	Description of the instrument/test	Scoring	Assessment timepoint	Clinically meaningful effect
Pain	Numeric Rating Scale (NRS)	A unidimensional instrument widely used to assess self-reported pain intensity.	0 (no pain) to 10 (worst pain imaginable).	T0, T1, and T2	Reduction of ≥ 2 points on the NRS.
	Digital pressure algometer	Assesses the pressure pain threshold in the bilateral peritraumatic region by applying gradually increasing pressure.	Value recorded in kgf/cm².	T0, T1, and T2	Increase in the pressure pain threshold.
Vulvar edema	Standardized photography and measuring tape	Objective assessment of vulvar edema using standardized photographic documentation and measurement of the edematous area.	Measurement in millimeters and photographic analysis.	T0, T1, and T2	Reduction in vulvar edema size.
Immediate postpartum functioning	Likert scale	Assesses difficulty in performing functional activities during the immediate postpartum period (standing up, sitting down, walking, and caring for the newborn).	1 = no difficulty to 5 = extreme difficulty.	T0, T1, and T2	Reduction in functional difficulty.
Patient satisfaction	Visual Analog Scale (VAS)	Assesses participant satisfaction with the treatment received.	0 = no satisfaction to 10 = maximum satisfaction.	T0 and T3	Increased satisfaction compared with the baseline assessment.
Global perceived change	Patient Global Impression of Change (PGIC)	Assesses the participant’s subjective perception of clinical improvement following the intervention.	1 = no change to 7 = very much improved.	T1 and T2	Score ≥ 5, indicating perceived improvement.
Late and remote postpartum functioning	World Health Organization Disability Assessment Schedule 2.0 (WHODAS 2.0)	Assesses functioning across six domains of daily life: cognition, mobility, self-care, getting along with others, life activities, and participation.	1 = no difficulty to 5 = extreme difficulty.	T3 and T4	Reduction in the total WHODAS 2.0 score.

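### The printed means and SDs give Cohen's d = 0.950, not the stated 0.784, and the higher pain score is assigned to the PBM arm

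*Protocol article*

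**What the plan says.** The Sample size calculation section plans for a "two-tailed independent-samples Student’s *t* test for the comparison of means between two independent groups". It sets "A significance level of 5% (α = 0.05), statistical power of 80% (1 − β = 0.80), and an allocation ratio of 1:1".

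The planning values are a "mean perineal pain score of 4.5 (SD = 3.0) was assumed for the experimental group and 2.0 (SD = 2.2) for the sham" group, taken from a cited earlier study, "resulting in an estimated effect size (Cohen’s *d*) of 0.784". From there the section arrives at 54 women (27 per group) with an actual power of 80.75%. It raises this to 68 (34 per group) for an expected dropout of 20%.

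Three other places bear on the direction of effect. Table 3 scores the NRS from 0 for no pain to 10 for the worst pain. The Expected outcomes section anticipates less perineal pain with PBM. The Introduction states the main objective as a reduction in pain, expressed as change from baseline.

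**The concern.** The article prints the inputs and the result side by side, and they disagree. Two means 2.5 points apart, with SDs of 3.0 and 2.2, imply a clearly larger standardised effect than 0.784. Since d determines the number of women, a reader needs to know whether the means and SDs or the d is the real planning assumption. As printed, the difference in NRS points that the trial was sized to detect cannot be recovered.

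The second difficulty is in the same sentence. The values are called pain scores, and the experimental arm has the larger one. On a scale where higher is worse, that is the reverse of the effect the trial expects.

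**Working it through.** **Inputs** (all from Sample size calculation): means 4.5 and 2.0; SDs 3.0 and 2.2; 1:1 allocation; two-sided alpha 0.05; target power 80%; dropout 20%. Power is from the exact noncentral t distribution for a two-sample t test, with n per group, df = 2n − 2 and noncentrality d × √(n/2).

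**1. The plan's own figures, starting from d = 0.784**
- n = 27: noncentrality 0.784 × √13.5 = 2.88, power 80.70%. The article gives 80.75%; a gap this small can come from rounding d to three decimals.
- n = 26: power 79.2%, so 27 is the smallest n that reaches 80%.
- Dropout: 54/(1 − 0.20) = 67.5, rounded up to 68.

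N, power and inflation all reproduce from the stated d.

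**2. The step from means and SDs to d**
- Pooled SD, equal groups: √((3.0² + 2.2²)/2) = √((9.00 + 4.84)/2) = √6.92 = 2.631.
- d = (4.5 − 2.0)/2.631 = 0.950.

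This step does not reproduce.

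**3. Could another convention give 0.784?**

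| Choice of denominator | d |
|---|---|
| Pooled SD, 2.631 | 0.950 |
| Pooled SD with Hedges correction | 0.937 |
| Average SD, 2.6 | 0.962 |
| Experimental SD alone, 3.0 | 0.833 |
| Sham SD alone, 2.2 | 1.136 |
| √(3.0² + 2.2²) = 3.720 | 0.672 |

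None does. Rounding does not explain it either. If each input moves to the edge of its one-decimal rounding interval, d runs from 2.4/√((3.05² + 2.25²)/2) = 0.90 to 2.6/√((2.95² + 2.15²)/2) = 1.01. To reach 0.784 with a 2.5-point difference, the common SD would have to be 2.5/0.784 = 3.19, larger than either printed SD.

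**4. What the printed means and SDs imply (d = 0.950)**
- Smallest n for 80% power: 19 per group (power 81.3%), 38 in total.
- With 20% dropout: 38/0.80 = 47.5, rounded up to 48.
- Power with 27 per group: 92.9%. A simulation with the unequal SDs gives 93.0% for the Student test and 92.9% for the Welch test.
- Power with 34 per group: 97.1%.

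**5. Direction.** PBM 4.5 against sham 2.0, read as scores on the NRS, is 2.5 points more pain with PBM. Read as reductions from baseline, or with the arms exchanged, the same numbers favour PBM. In a two-sided test d enters only through its absolute value, so steps 1 to 4 are the same under every reading.

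**The case against.** The best defence is that the section also states d, and that everything after d is coherent: 27 per group, about 80.7% power and 68 after dropout. That is correct. It confines the fault to one link, and it would be wrong to say that N and power have no stated basis.

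On direction, a reader might infer that the trial was planned on PBM being worse than sham, against its own superiority aim. The article does not support that. It expects less pain with PBM, and it frames the objective as change from baseline, so the figures may well be reductions with the larger one in the PBM arm. What remains is that the sentence calls them scores and says neither that they are changes nor that the labels are exchanged.

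A reader might also infer that the trial is underpowered. Neither stated basis shows that. If d = 0.784 is right, 54 evaluable women suffice; if the printed means and SDs are right, 38 do.

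Finally, it is tempting to test the design against the entry in Table 3, "Reduction of ≥ 2 points on the NRS". That entry describes a reduction in score. It is not stated as a between-group difference in means, so power for a 2-point difference between arms does not test any target that the article sets.

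**Conclusion.** The point holds as an error of arithmetic and labelling in the sample size paragraph. The printed inputs give d = 0.950 where the article states 0.784. In planning terms the gap is 19 against 27 women per group, or 92.9% against about 80.7% power with 27 per group.

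The article does not show which figure is wrong, and the cited source was not available to settle it. The assigned direction conflicts with the expected benefit unless the values are reductions or the arm labels are exchanged, and it has no effect on N. The conclusion rests on the usual pooled-SD definition of Cohen's d; the other definitions tried do not rescue 0.784.

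The planned 68 women are enough on either stated basis. This is a wrong planning figure that should be corrected, not evidence of a design that is too small.

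**What to change.** Go back to the cited source and recheck the two means and SDs. State whether they are pain scores or changes from baseline, at which time point, and which arm each belongs to. Correct whichever of the means, SDs or d is wrong, so that d follows from the printed inputs. Then restate the effect size, the between-group difference in NRS points, and the power that the planned 68 women give, both in full and after 20% dropout.

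The difference in points should come from the rechecked source. Multiplying 0.784 by the SD of 2.631 would combine two figures that contradict each other, and would fit the rationale to the sample size.

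The cost is one rewritten paragraph. On either basis now printed, the sample size need not rise. If the recheck yields a d below 0.784, the adequacy of 68 would have to be looked at again.

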### Randomization and allocation concealment

Participants will be randomized in blocks of four according to a sequence of random numbers ranging from 1 to *x* (the total number of participants to be randomized), generated using Random Allocation Software version 1.0. An independent researcher not involved in participant recruitment, intervention delivery, outcome assessment, or data analysis will generate the randomization sequence and prepare sequentially numbered, opaque, sealed, and stapled envelopes containing the treatment allocation, in accordance with the CONSORT recommendations (Fig. 1) [17].

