### Intervention

The study will comprise two groups: (G1) photobiomodulation (PBM) and (G2) sham PBM, with both groups receiving usual postpartum care. Women diagnosed with first- and/or second-degree perineal trauma and/or obstetric vulvar edema will be invited to participate and randomly assigned to one of the two study groups.

A single treatment session will be performed during the immediate postpartum period, within 12 h after childbirth, with an approximate duration of 20 min. Before the intervention, participants will undergo the baseline assessment, including evaluation of perineal pain using the Numeric Rating Scale (NRS). In both groups, participants will receive individualized care and standardized education regarding pelvic floor anatomy, perineal trauma, vulvar edema, and perineal care. At the end of the immediate postpartum assessment, all participants will receive an educational leaflet containing recommendations for perineal care.

Participants allocated to G1 will receive PBM using the TERAPY-EC^®^ device with a wavelength of 808 nm (infrared), output power of 100 mW, beam area of 1 mm², and power density of 1.02 W/cm².

For participants presenting with first- and/or second-degree perineal trauma and pain ≥ 3 on the NRS, infrared light (808 nm) will be applied using a point-by-point technique, with an energy density of 60 J/cm² for 60 s per application point, corresponding to 6 J of energy per point. The irradiation will be performed around the perineal lesion and along the course of the pudendal nerve. One or two irradiation points will be used according to the size and extent of the lesion, with the exact number of points documented for each participant.

For participants presenting with both perineal pain and vulvar edema, the complete perineal pain protocol described above will be performed first. Subsequently, PBM will be applied to the edematous vulvar area using 808-nm infrared light at an energy density of 10 J/cm² for 10 s per point, with a 2-cm distance between adjacent application points. In addition, two irradiation points will be applied to the inguinal region, with 20 J/cm² per point, corresponding to 20 s per point, for a total of 40 J/cm² and 40 s in the inguinal region. The treatment sequence will therefore consist of perineal irradiation first, followed by irradiation of the edematous vulvar area and, finally, the two inguinal points, when vulvar edema is presente (Table 2).

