**Table 2 Tab2:** Photobiomodulation intervention parameters for perineal pain and vulvar edema

Parameter	Perineal pain	Vulvar edema
Clinical condition	First- and/or second-degree perineal trauma + pain ≥ 3 on the NRS	Obstetric vulvar edema
Wavelength	808 nm (infrared)	808 nm (infrared)
Output power	100 mW	100 mW
Beam area	1 mm²	1 mm²
Power density	1.02 W/cm²	1.02 W/cm²
Application technique	Point-by-point	Point-by-point
Energy density	60 J/cm²	10 J/cm²
Application time	60 s per point	10 s per point
Energy per point	6 J	1 J
Number of points	1–2 points, according to lesion size	According to the extent of the edematous area
Application site	Around the lesion and along the course of the pudendal nerve	Over the edematous vulvar area
Distance between points	—	2 cm
Additional application	—	2 points in the inguinal region
Parameter for inguinal points	—	20 J/cm² per point
Application time at inguinal points	—	20 s per point
Energy at inguinal points	—	2 J per point
Total energy at inguinal points	—	4 J
Treatment sequence	Application around the lesion and along the pudendal nerve pathway	Edematous area → inguinal region

Note: For participants presenting with both perineal pain and vulvar edema, the perineal pain protocol will be performed first, followed by application to the edematous area and, subsequently, to the two inguinais points

Participants allocated to G2 will undergo the same application procedure, positioning, treatment sequence, and approximate treatment duration as participants in G1. However, the device will remain inactive, with no light emission, thereby providing a sham intervention. The same device and application sites will be used to maintain participant blinding. Participants in the sham group will also receive the same standardized postpartum education and usual care provided to the PBM group.

All intervention procedures will be performed by trained physiotherapists following a standardized operating procedure (SOP). The parameters, number and location of application points, duration, and energy delivered will be recorded for each participant to ensure treatment fidelity and reproducibility.

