### Statistical analysis

Statistical analyses will be performed using the Statistical Package for the Social Sciences (SPSS), version 20.0 (IBM Corp., Armonk, NY, USA), adopting a significance level of 5% (*p* < 0.05). Descriptive statistics will be presented as absolute and relative frequencies for categorical variables and as means, standard deviations (SD), and 95% confidence intervals (95% CI) for continuous variables.

The primary analysis of longitudinal outcomes will be performed using linear mixed-effects models. Treatment group (photobiomodulation and sham), time (T0: baseline; T1: immediately after the intervention; T2: 12 h after the intervention; T3: 40 days postpartum; and T4: 3 months postpartum), and the group × time interaction will be included as fixed effects, while participant will be included as a random effect to account for the correlation among repeated measurements within the same participant. The group × time interaction will be considered the primary parameter for determining whether changes in outcomes over time differ between the photobiomodulation and sham groups. Baseline outcome values will be included in the model when appropriate.

Model assumptions will be assessed by examining the distribution of residuals and the homogeneity of variance. If substantial deviations from model assumptions are identified, appropriate data transformations or alternative statistical approaches will be considered.

For baseline comparisons, categorical variables will be analyzed using Pearson’s chi-square test or Fisher’s exact test, as appropriate. Continuous variables will be analyzed using the independent-samples Student’s t-test for approximately normally distributed data or the Mann–Whitney U test for non-normally distributed data.

When a significant group × time interaction is identified, post-hoc pairwise comparisons will be performed to determine differences between groups at each assessment time point and changes within each group over time. The Bonferroni correction will be applied to adjust for multiple comparisons and control the family-wise type I error rate.

The magnitude of the intervention effect will be estimated using mean differences (MD) for continuous outcomes and relative risks (RR) for dichotomous outcomes, with corresponding 95% confidence intervals (95% CI). The number needed to treat for benefit (NNTB) will be calculated for dichotomous outcomes when applicable.

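### Edema status shapes the treatment and defines who informs the edema objective, but it is neither a stratification factor nor a model term; a chance imbalance would do modest harm and is cheap to guard against

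*Protocol article*

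**What the plan says.** The inclusion criteria admit women with "first- and/or second-degree perineal trauma and/or vulvar edema", all with pain of at least 3 on the NRS. Under Intervention, every woman with perineal trauma receives the perineal points. Where edema is also present, further sites are added: "Subsequently, PBM will be applied to the edematous vulvar area using 808-nm infrared light", and then two inguinal points. The same section gives the order, with perineal irradiation "followed by irradiation of the edematous vulvar area and, finally, the two inguinal points, when vulvar edema is presente". The sham arm mirrors this: "Participants allocated to G2 will undergo the same application procedure, positioning, treatment sequence, and approximate treatment duration as participants in G1".

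Randomization and allocation concealment describes a single numbered sequence ("Participants will be randomized in blocks of four according to a sequence of random numbers") and names no stratification factor. Statistical analysis lists treatment group, time "and the group × time interaction will be included as fixed effects", with participant as a random effect, and makes the interaction the primary parameter. The only adjustment mentioned is "Baseline outcome values will be included in the model when appropriate".

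The Introduction makes vulvar edema a secondary objective, and Table 3 measures it at T0, T1 and T2. No expected number of women with edema is given.

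**The concern.** Edema at T0 plays three roles. It determines which version of the procedure a woman receives, it identifies the women who can show a reduction in edema, and it may plausibly affect pain. Blocks of four on one list keep the total arm sizes equal but do not control how women with edema divide between the arms.

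Two things are at stake. An uneven split of the edema subset costs precision for that secondary outcome. If women with edema also recover from pain at a different rate, an uneven split shifts the pain comparison, and the stated model has no term to remove the shift.

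**Working it through.** **Inputs from the protocol.** The sample size section gives d = 0.784, 27 per group, 80.75% power and 20% dropout, hence 68 women. At d = 0.784 and 27 per group, a two-sided t test has power 80.70%, which agrees with the stated figure to rounding. Then 54 / 0.8 = 67.5, rounded up to 68, or 34 per arm and exactly 68 / 4 = 17 blocks.

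**Assumption.** Edema prevalence is not given; 20% to 50% is used as a range.

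**Chance imbalance.** Lists of 17 permuted blocks of four were simulated 100,000 times, with edema assigned independently of arm. With a and b the edema cases in the two arms:

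| Assumed prevalence | Mean edema cases | P(gap ≥ 4) | P(gap ≥ 6) | Mean efficiency |
|---|---|---|---|---|
| 20% | 13.6 | 28.5% | 9.4% | 0.935 |
| 30% | 20.4 | 35.1% | 14.4% | 0.963 |
| 50% | 34.0 | 39.8% | 18.3% | 0.985 |

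A separate run of 40,000 lists gave 28.7%, 35.4% and 39.4% for a gap of four or more, and 9.1%, 14.5% and 18.2% for six or more.

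**Cost for the edema outcome.** Efficiency relative to an equal split is 4ab / (a + b)². The means above are losses of 6.5%, 3.7% and 1.5%. For individual splits of 20 women:
- 12 versus 8: 4 × 96 / 400 = 0.96, so the standard error grows by 1/√0.96 − 1 = 2%.
- 13 versus 7: 4 × 91 / 400 = 0.91, so it grows by 1/√0.91 − 1 = 5%.

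**Cost for pain.** If edema alters the change in NRS by g points, a gap of k cases shifts the group contrast by g × k / 34. With g = 1 (assumed), a gap of 4 gives 4/34 = 0.12 points and a gap of 6 gives 6/34 = 0.18. For g between 0.5 and 2, a gap of 6 gives 0.09 to 0.35. Table 3 regards a reduction of 2 points as meaningful.

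If edema only raises pain by a constant amount at every visit, the shift is already present at T0 and cancels in the change from baseline, which is what the interaction measures.

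**What a covariate does.** With complete data and a random participant intercept, the interaction is estimated from within-participant contrasts, to which a time-constant covariate contributes nothing. This was checked by fitting the stated model to simulated data (68 women, edema split 13 versus 7, edema adding one NRS point, T0 to T2). The two interaction estimates were −0.990229 and −1.797309 both without and with an edema main effect; the standard errors were 0.40839 and 0.40838. With 20% missing at T2, the T2 estimate moved by 0.01. To act on the primary parameter, edema must therefore enter with edema × time, or enter a model of T1 and T2 that conditions on the baseline value.

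**What stratification does.** Within a stratum, blocks of four allow a gap of at most 2 women, or 2/34 = 6 percentage points.

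**The case against.** The strongest reply is that unstratified permuted blocks are valid in a single-center trial of 68 women, that chance imbalance is already reflected in the standard errors, and that covariate lists are often left to an analysis plan. Validity is not in dispute. But the article does state both the allocation scheme and the fixed effects, and an analysis plan cannot add stratification after allocation.

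Three stronger readings are tempting, and the documents support none of them.
- A reader might infer that the extra irradiation given to women with edema confounds the pain comparison. It does not: the sham follows the same sequence, so edema-dependent content belongs to the assigned strategy in both arms. A different effect in women with edema would be effect modification.
- A reader might infer that the edema comparison does rest on an unbalanced subset. Randomization balances edema in expectation; imbalance is only a possibility.
- A reader might infer that the analysis ignores edema altogether. For the edema outcome, the optional baseline adjustment would bring in baseline edema area. For pain it brings in baseline pain, not edema status.

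It also stands that a stable pain difference between women with and without edema cancels in the interaction, and that the average costs are small.

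**Conclusion.** The point holds as a low-cost improvement and does not threaten the trial's validity. A factor that determines treatment content and defines the informative subset for a secondary objective is absent from both the randomization and the stated model. By chance, the arms may differ by four or more edema cases in roughly 29% to 39% of lists and by six or more in 9% to 18%. The expected efficiency loss for edema is about 1.5% to 6.5%. Pain contrasts would shift by a few tenths of an NRS point at most over the values examined, and only if edema affects the pain trajectory.

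These sizes rest on an assumed prevalence of 20% to 50%, on 68 women randomized, and on an assumed edema effect on pain change of 0.5 to 2 points.

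The size of the edema subset matters more than its split. For an effect as large as the one assumed for pain (d = 0.784), equal arms drawn from 68 women give power of about 27%, 38% and 60% at prevalences of 20%, 30% and 50%. Stratification does not cure that.

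**What to change.** Table 1 gives enrollment as July 2025 to December 2026, so the remedy depends on whether allocation has begun.

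- **Not started:** prepare two envelope series in blocks of four, for edema present and edema absent, with edema recorded by the blinded assessor at T0 before an envelope is opened.
- **Started:** keep the existing list. Before unblinding, prespecify edema at T0 (yes/no) together with edema × time in the NRS and pressure pain threshold models. Alternatively, include edema at T0 in a model of T1 and T2 that adjusts for the baseline value. An edema main effect on its own is not enough.

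The cost is a second envelope series with possibly one incomplete block in each. Total arm sizes could then differ by up to 2 + 2 = 4 women. The model terms use 1 + 2 = 3 degrees of freedom over T0 to T2, or one in the baseline-adjusted version. Edema is already assessed at T0, so no additional participants or procedures are needed.
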